
#### Power Calculation

4.4.2

Sample size was calculated using the swCRTdesign package in RStudio.

Parameters:

*Stepped wedge design*: As shown in Figure 1.
*Primary endpoint*: 30‐day mortality.
*Design*: Non‐inferiority trial.
*Number of patients per cluster and time period*: A total of 38 ICUs were included in the analysis. Two ICUs were merged into a single cluster because they share staff, resulting in *37 distinct clusters*. The stepped‐wedge design comprised *13 time periods*. Based on historical data, the total number of ICU admissions during the 13‐month study period was estimated to be *22,625 episodes*, derived from Swedish Intensive Care Registry admission data for the participating clusters over the corresponding calendar period [29]. Under these assumptions, the average number of ICU admissions per cluster and time period was calculated as 22,625 ÷ 13 ÷ 37 ≈ *47 admissions*.These are the parameters prespecified before recruitment opened. Following the withdrawal of one cluster, the corresponding figures are 22,428 episodes across 36 clusters and 13 periods, approximately 47 admissions per cluster‐period, a reduction of 0.9% that does not materially affect the power calculation, which has therefore not been repeated.
*Alpha level*: 0.025 (one‐sided 97.5% CI).
*Intraclass correlation coefficient (ICC)*: 0.009
○The ICC was calculated using historic data via a generalized linear mixed model. To account for differences in baseline mortality across ICU types, the model included:
A variable distinguishing ICU category [1, 2, 3].A variable indicating whether the ICU was a thoracic unit, which has distinct expected mortality rates.

*Treatment effect was assumed to be homogeneous across clusters*.
*No fixed time trends were assumed*.

*Non‐inferiority margin assumption for 30‐day mortality*: Based on historical data, the mean baseline 30‐day mortality across the relevant clusters was estimated at 18%, based on Swedish Intensive Care Registry historical data for the participating clusters [29]. The non‐inferiority margin was defined as an absolute risk difference of 3 percentage points. Assuming the same baseline mortality, this corresponds to a relative risk of 1.17 and an odds ratio of approximately 1.21.

*Power to demonstrate non‐inferiority under the assumptions stated above*: 89%. A Power > 80% will be considered acceptable to demonstrate non‐inferiority.

### Randomization and Allocation

4.5

#### Cluster Definition

4.5.1

Individual ICUs represent clusters for randomization purposes, with one exception: where two ICUs have physicians and nurses working at both ICU sites in the same hospital. These two interconnected ICUs are seen as one cluster. SIR categorizes ICUs into Levels 1, 2, and 3 based on care level [36].

ICUs in Category 1 manage intensive care for patients with failure in all organ systems but lack most supporting resources. The hospital lacks access to most specialties and resources around the clock, for example, pediatrics, vascular surgery, ENT surgery, and blood bank. ICUs in Category 1 should be able to consult and send patients for care at ICUs in Categories 2 and 3. For this to work, ICUs in Category 1 must be able to receive patients with less complex needs from Category 2 and 3 units.

ICUs in Category 2 manage intensive care for patients with failure in all organ systems but lack Category 3's supporting resources. The hospital can still function as a referral center for the region, for example, for specialties such as pediatrics, vascular surgery, angiographic services, and/or ENT surgery. They therefore have access to most specialties, particularly emergency surgery, radiology, laboratory, and blood bank around the clock. ICUs in Category 2 should be able to consult and send patients for care at ICUs in Category 3. For this to work, units within Category 2 must be able to receive patients with less complex needs from Category 3 units.

Category 3 consists primarily of ICUs at university hospitals. These provide the most advanced monitoring and treatment methods for various types of organ failure. Since this category typically represents the full capacity of Swedish healthcare, they serve as referral centers for smaller hospitals. ICUs within Category 3 should have a system to oversee all the hospital's intensive care resources and have clear communication pathways into the hospital, preferably with a lead intensive care physician who can be reached on a dedicated phone line from referring hospitals. To function as a referral center with preparedness to receive the most complex patients regardless of place of residence, ICUs in Category 3 must also be able to transfer less complex intensive care patients to Category 1 and 2 units in the surrounding area.

#### Randomization Scheme

4.5.2

The 37 clusters were randomized to 1 of the 10 implementation sequences, with three or four clusters allocated per sequence; this restricted allocation ensures a balanced stepped‐wedge layout across the 13 monthly periods. The allocation sequence was generated by a constrained randomization algorithm implemented in R (version 4.6) with a fixed random seed. The seed, the generating script, and equivalent implementations in Stata and Python have been archived and will be made available with the trial report, allowing full reproduction of the allocation. Randomization was stratified by ICU category and ICU size (admissions/year). One prespecified constraint was applied: the two ICUs sharing staff at the same hospital were treated as a single cluster and therefore necessarily follow the same sequence. The sequence was created by [name], who had no clinical role at any participating unit. Because randomization was at the cluster level and no individual patient was enrolled, there were no enrolling personnel whose behavior could be influenced by foreknowledge of the next allocation, and conventional allocation concealment is not applicable in the individual‐participant sense. The generated sequence was not disclosed to participating units before allocation was complete; each cluster was subsequently informed of its own transition date 6–8 weeks in advance, as described above. The full allocation list is stored securely with the trial master file.

## Statistical Analysis Plan

5

### General Principles

5.1

Analysis of the primary outcome follows the intention‐to‐treat principle, with every care episode analyzed according to the randomized state of its cluster at the time of admission and irrespective of local adherence; a prespecified per‐protocol analysis is reported alongside it.Mixed‐effects models will account for clustering and temporal trends.Multiple imputation will address missing data when > 10% are missing for key covariates.Sensitivity analyses will explore the robustness of findings.Statistical significance will be set at *α* = 0.05 for superiority analyses and *α* = 0.025 (one‐sided) for non‐inferiority analyses.

No adjustment for multiplicity is made. Only the primary outcome supports a confirmatory conclusion; secondary, process, and exploratory outcomes are reported as point estimates with 95% confidence intervals (CIs) and interpreted as supportive, with no formal non‐inferiority testing applied to them.

### Primary Analysis—Mortality (Non‐Inferiority)

5.2

The primary analysis fits a generalized linear mixed‐effects model for 30‐day mortality with a binomial distribution and logit link. The model includes a fixed effect for treatment condition (intervention versus control), fixed effects for calendar time modeled as categorical monthly periods, fixed‐effect adjustment for the prespecified baseline covariates (SAPS 3 score, age, sex, admission type [emergency vs. planned], and ICU category [SIR Levels 1–3]), and a random intercept for cluster, implying an exchangeable within‐cluster correlation structure. Sensitivity analyses will explore alternative correlation structures, including a random cluster‐by‐period effect allowing the within‐period correlation to exceed the between‐period correlation. Because a minority of patients contribute more than one care episode, the model also includes a random intercept for patient nested within cluster. A sensitivity analysis restricted to each patient's first ICU admission during the study period will be reported.

Because the estimand is an absolute risk difference, adjusted marginal risks under intervention and control are obtained from the fitted model by regression standardization (g‐computation): the model is used to predict each episode's outcome probability under both treatment conditions, and these predictions are averaged over the trial population. The adjusted risk difference is the difference between the two standardized risks, with a 95% CI obtained by cluster bootstrap or delta method. Non‐inferiority is declared if the upper bound of the two‐sided 95% CI (equivalently the one‐sided 97.5% bound) for the adjusted risk difference (intervention minus control) lies below 3 percentage points. Intention‐to‐treat analysis behaves differently in a non‐inferiority trial than in a superiority trial. Whereas incomplete adherence biases a superiority comparison toward the null and is therefore conservative, in a non‐inferiority comparison it makes the two conditions more alike and so makes a conclusion of non‐inferiority easier to reach; intention‐to‐treat is in this sense anti‐conservative [37]. We therefore prespecify a per‐protocol analysis alongside the primary intention‐to‐treat analysis. The per‐protocol population comprises all control periods together with those intervention cluster‐periods in which the cluster's own testing intensity met the fidelity criterion; cluster‐periods during which the intervention was paused or modified under the provisions above are excluded from the intervention condition. The per‐protocol analysis uses the same model, covariates, and non‐inferiority margin as the primary analysis. A conclusion of non‐inferiority requires the upper confidence bound to lie below the margin in both analyses. Where the two are discordant, both are reported, and the discordance is discussed rather than resolved by rule. Realized testing intensity is reported for both conditions at cluster level so that the separation achieved is visible to the reader.

ICU length of stay and the durations of invasive ventilation, noninvasive ventilation, and CRRT are analyzed in a time‐to‐event framework, with time origin at ICU admission (for length of stay) or at initiation of the respective therapy (for therapy durations). The events of interest are, respectively, live ICU discharge and liberation from the therapy; death before the event is treated as a competing event using cause‐specific Cox proportional‐hazards models with a gamma‐distributed cluster‐level frailty to account for clustering, complemented by cause‐specific cumulative incidence functions. Episodes are administratively censored at 30 days from ICU admission for length of stay, and from initiation of the respective therapy for the durations of invasive ventilation, noninvasive ventilation, and CRRT; episodes still ongoing at that point are censored. Treating death as a competing event rather than censoring avoids the bias whereby early deaths masquerade as short, favorable stays. Proportional‐hazards assumptions are assessed with Schoenfeld residuals; where violated, effects are reported as time‐varying or summarized as restricted‐mean‐survival‐time differences. Models are adjusted for the same covariates as the primary analysis. Unplanned ICU readmission within 72 h is analyzed among live ICU discharges with a logistic generalized linear mixed‐effects model specified analogously to the primary analysis.

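### The non-inferiority bound comes from a model without a cluster-by-period effect and from an interval method left open, so it can be modestly too narrow in the direction that favours non-inferiority

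*Protocol article*

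**What the plan says.** Primary Analysis—Mortality (section 5.2) specifies a logistic mixed model with treatment, categorical monthly periods, SAPS 3, age, sex, admission type and ICU category. It has "a random intercept for cluster, implying an exchangeable within‐cluster correlation structure" and a second random intercept for patient within cluster, to handle repeat episodes. A random cluster-by-period effect is listed among the sensitivity analyses. Section 5.4 again promises alternative correlation structures as sensitivity analyses. Nowhere does the result of such an analysis enter the non-inferiority decision.

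The adjusted risk difference is obtained by standardization, "with a 95% CI obtained by cluster bootstrap or delta method". Non-inferiority requires the upper limit to lie below 3 percentage points. The per-protocol analysis uses the same model and margin, and its bound must also lie below 3 points. Power Calculation (section 4.4.2) uses a single ICC of 0.009, with no split between within-month and between-month correlation, and states 89% power.

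**The concern.** An exchangeable intercept treats two patients in the same ICU as equally correlated whether they were admitted in the same month or a year apart. Staffing, case mix and seasonal load can make a month's patients more alike than that. The treatment contrast in a stepped wedge draws heavily on month-to-month change within clusters. Unmodelled month-level variation is then treated as patient-level noise that averages out, and the model-based standard error is too small. In a non-inferiority test that error runs in the unsafe direction.

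The open choice of interval method makes this matter. Resampling whole clusters carries the true within-cluster correlation into the interval, whatever the model assumes. A delta method applied to the mixed model's own covariance does not. The two permitted methods therefore diverge just when the exchangeable assumption fails, and the plan does not say which bound decides.

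**Working it through.** **Inputs from the article.** One-sided alpha 0.025. On the margin: "The non‐inferiority margin was defined as an absolute risk difference of 3 percentage points". Baseline mortality 18%, ICC 0.009, 13 periods, 10 sequences. Planned: 37 clusters with 47 admissions per cluster-month. After the withdrawal: 36 clusters and 22,428 episodes, so n = 22,428 / (36 × 13) = 47.92.

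**Assumptions.** Figure 1 is not shown, so the ten sequences are taken to switch at the start of months 2 to 11, with the four-cluster sequences placed first. The cluster autocorrelation (CAC, between-month divided by within-month correlation) is not in the article; 0.9 to 0.5 is an assumed range. The calculation is a linear approximation on cluster-month means, without patient covariates.

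**Step 1: the plan's own figure.** Generalized least squares with period effects and an exchangeable intercept; cluster variance = ICC/(1 − ICC) × σ²; power = Φ(0.03/SE − 1.96); 37 clusters, n = 47.
- σ² = 0.21 × 0.79: SE 0.00934, power 89.5%. This reproduces the stated 89%.
- σ² = 0.18 × 0.82: SE 0.00881, power 92.6%.
- With no period effects in the model, power exceeds 99.8%.

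The stated 89% therefore matches a model with period effects and a purely exchangeable correlation.

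**Step 2: the variance left out.** With σ² = 0.18 × 0.82 = 0.1476, the total cluster variance is 0.009/0.991 × 0.1476 = 0.00134. Split it as τ² = CAC × 0.00134 (cluster) and γ² = (1 − CAC) × 0.00134 (cluster-by-month). At CAC 0.5, γ² = 0.00067. Patient sampling contributes 0.1476/47.92 = 0.00308 to the variance of a cluster-month mean, so the omitted part is about 22% of that.

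**Step 3: error rate.** The true covariance of a cluster's 13 monthly means is V = (γ² + σ²/n)I + τ²J. The exchangeable model instead uses V_w = ((γ² + σ²)/n)I + τ²J. With D_k holding the period indicators and treatment for cluster k, and A = Σ D_k′V_w⁻¹D_k, the model-based variance is the treatment element of A⁻¹. The true variance is the treatment element of A⁻¹(Σ D_k′V_w⁻¹VV_w⁻¹D_k)A⁻¹. One-sided error at the margin = Φ(−1.96 × SE_model/SE_true). The last column is the power when the cluster-by-period effect is modelled.

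| ICC | CAC | SE_model | SE_true | Ratio | Error | Power, effect modelled |
|---|---|---|---|---|---|---|
| 0.009 | 1.0 | 0.00884 | 0.00884 | 1.000 | 2.50% | 92.4% |
| 0.009 | 0.9 | 0.00881 | 0.00898 | 1.019 | 2.73% | 91.6% |
| 0.009 | 0.8 | 0.00877 | 0.00911 | 1.038 | 2.95% | 90.9% |
| 0.009 | 0.5 | 0.00860 | 0.00938 | 1.091 | 3.62% | 89.3% |
| 0.02 | 1.0 | 0.00903 | 0.00903 | 1.000 | 2.50% | 91.3% |
| 0.02 | 0.9 | 0.00902 | 0.00943 | 1.045 | 3.03% | 88.9% |
| 0.02 | 0.8 | 0.00901 | 0.00979 | 1.087 | 3.57% | 86.5% |
| 0.02 | 0.5 | 0.00892 | 0.01071 | 1.201 | 5.14% | 80.3% |

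Leaving γ² out of the working residual moves the errors by no more than about 0.1 point (3.65% and 5.22% in the two CAC 0.5 rows). The errors depend only on the ratio of standard errors, so they are the same whether σ² is taken at 18% or 21%.

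**Step 4: simulation.** With 4,000 simulated trials at ICC 0.009 (Monte Carlo standard error about 0.25 points), the error was 2.4% with no cluster-by-period effect, 2.2% at CAC 0.8 and 3.7% at CAC 0.5. The inflation is confirmed at 0.5. At 0.8 the simulation shows none and lies below the analytic 2.95%.

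**The case against.** Several points on the other side carry weight.

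- **The structure is already named as a sensitivity analysis, and the CAC range is assumed.** Both are true, and at the planning ICC mild departures have little effect. But a sensitivity analysis without a decision role cannot change the declaration.
- **A delta method can be applied to a robust covariance.** It can, but section 5.2 does not say so, and from a fitted mixed model the default covariance is model-based.
- **The choice cannot follow the results.** The Blinding section has the code finalized and archived before the exposure coding is revealed. That stands, and it limits result-driven selection. It does not say which bound is prespecified. Trial Status mentions a fuller deposited plan, which may settle the matter, but it also presents this article as the analysis plan, and the article states the alternative.
- **The practical harm is limited.** The Discussion says in advance that a point estimate of excess mortality would not support de-implementation. With a true 3-point harm and an SE of 0.00938, an estimate at or below zero has probability Φ(−0.03/0.00938) = Φ(−3.20), about 0.0007. The formal declaration is exposed; a change in practice is hardly so.

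A reader might also infer that everything rests on one upper bound. It does not. The per-protocol bound must also pass, and section 4.3.1 requires at least a 5% reduction in testing. These conditions can only lower the chance of a false declaration. However, the per-protocol bound comes from the same model and has the same defect, and the fidelity condition says nothing about uncertainty in mortality.

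A second tempting inference concerns omitted covariates. "Randomization was stratified by ICU category and ICU size (admissions/year"), yet size is not in the model. The planning ICC was estimated with "A variable indicating whether the ICU was a thoracic unit, which has distinct expected mortality rates", which is also absent. Neither omission threatens the 2.5%. The cluster intercept absorbs differences that are constant over time, and simulation without a strong thoracic-type term gave 2.6% against 2.4% when no such term was present. The residual ICC could be above or below 0.009, since the primary model also adds patient covariates.

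**Conclusion.** The point holds with a modest size. The primary model has no cluster-by-period effect and the deciding interval method is not fixed. With a model-based delta-method interval, the one-sided error at the margin is about 2.7 to 3.6% at ICC 0.009, and about 3.0 to 5.1% if the ICC were 0.02, for an assumed CAC of 0.9 to 0.5. With a cluster bootstrap the problem largely disappears, which is why the choice should be stated. The figures rest on the assumed CAC, the assumed switch months, equal cluster-month sizes and a linear approximation. The documents do not support a claim that the error rate is badly out of control, nor that the missing ICU-size and thoracic terms contribute to it.

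**What to change.** 1. Put the random cluster-by-period effect in the primary model, for both the intention-to-treat and the per-protocol analysis. Keep the exchangeable-only model as a sensitivity analysis, and state the fallback if the variance is estimated at zero.
2. Name one interval method for the decision: cluster-level resampling, or a cluster-robust interval with a small-sample correction for 36 clusters.
3. Optionally, add ICU size and the thoracic indicator, or explain their absence. This is for consistency with the stratification and the planning ICC, not for error control.

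**Cost.** The interval becomes slightly wider. At ICC 0.009, power falls from 92.4% to between 91.6% and 89.3%. At ICC 0.02 it falls from 91.3% to 88.9% (CAC 0.9), 86.5% (0.8) or 80.3% (0.5). These use σ² at 18%. On the 21% basis that reproduces the stated 89%, every SE is multiplied by √(0.1659/0.1476) = 1.060. Power then goes from 89.3% to between 88.3% and 85.5% at ICC 0.009, and from 88.0% to between 85.1% and 75.6% at ICC 0.02. Only that last corner falls below the plan's 80% criterion. Bootstrap run time is a further small cost.

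Protocol Amendments (section 6.2) treats a change to the analysis plan as substantive, so ethics-authority approval and a registry update are needed. Trial Status says that all versions were finalized before outcome data were extracted or examined. If that is still the position, the change can be prespecified.
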